**Fig. 2 Fig2:**
[figure not shown]
Schedule of enrollment, interventions, and assessments (Standard Protocol Items: Recommendations for Interventional Trials (SPIRIT) figure). Note that the assessment of covariates is not depicted here

The close monitoring of the patients by the trained research assistants ensures a high level of adherence to the study protocol. Nevertheless, deviations from the study protocol may occur, for two main reasons: (1) If the research assistants supervising the patients notice excessive psychological strain on the part of the patient, the study procedure will be discontinued or interrupted until the patients’ mental state is stable enough to continue. (2) In case of medical complications, e.g., due to adverse events of the therapy, the follow-up (T_2_) can be rescheduled to an earlier date. In general, the follow-up measurement will take place at slightly different time points, depending on the patient’s staging appointment for a medical checkup. Deviations of 2 weeks before and after the 12th week after the intervention will be tolerated for the follow-up. All other deviations, including those resulting from the abovementioned reasons, will be documented and taken into account in a sensitivity analysis. To audit trial conduct, the study administration (CB and PG) will organize monthly meetings with study physicians and research assistants as well as regular site visits and controls of data quality. This way, corrective actions can be initiated when necessary. Important changes to the study protocol will be communicated to the sponsor as well as to the responsible ethical committee and registered on ClinicalTrials.gov. For organizational reasons, audit measures (except for controls of data quality) will be carried out by a study nurse at the study center in Dresden.

The names of the patients and all other confidential information will be subject to medical confidentiality and the provisions of the Federal Data Protection Act. Third parties will not have access to the original medical records. Each study center will be independently responsible for data collection. All data will be pseudonymized, including the patients’ entries on the PtDA website, which will be transferred to the study centers as an e-mail attachment (PDF document). The questionnaire data collected at the study center in Dresden will be sent by post to Heidelberg, while audio recordings will be transmitted to Heidelberg via the cloud. Data storage, entry, and analysis will be carried out exclusively in Heidelberg. All study data will be treated as strictly confidential and will be evaluated exclusively by the study staff. The data will be stored for 15 years after the completion of the study. The results will be made available to the public by publishing them in a peer-reviewed journal. It will be ensured that no inference can be made about the identity of participants.

### Statistical analysis

#### Sample size

A power analysis was conducted with GPower version 3.1.9.2 with patients’ knowledge about first-line treatment options at T_1_ as the main outcome for the effectiveness of the intervention. According to a Cochrane review, PtDAs improve the level of knowledge with an effect size of *d* = 0.60 [25]. On the basis of a group comparison (*t* test for independent samples) and an *α* error of 5% (two-sided), a case number of *n* = 45 participants per group (total = 90) is sufficient to detect a statistically significant effect of *d* = 0.6 with a power of 80%. To compensate for an assumed drop-out rate of approximately 40%, we plan to include 128 patients in the study.

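### The planned 128 patients and the assumed drop-out of about 40% do not fit together: 128 leaves the required 90 evaluable patients only up to about 30% loss

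*Protocol article*

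**What the plan says.** The Sample size section of the protocol article bases the trial size on knowledge of first-line treatment options at T1. The inputs are a standardised effect of d = 0.60 from a Cochrane review, a two-sided alpha of 5%, 80% power and a t "test for independent samples". The result is that "45 participants per group (total = 90) is sufficient to detect" that effect. The next sentence gives the enrolment target: "To compensate for an assumed drop-out rate of approximately 40%, we plan to include 128 patients in the study". No derivation of 128 is shown. The Abstract repeats 128 as the number to be randomised, and the Randomization section sets 1:1 allocation.

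The Main analyses section plans something other than the test used for sizing. The primary analysis is a linear regression of T1 knowledge on group, adjusted for T0 knowledge, age, education and study center. It is run in the intention-to-treat population (without patients who withdraw consent), with multiple imputation under missing at random.

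**The concern.** The 90 patients are those needed with an outcome, and the 128 are those to be randomised. If the second number is meant to protect the first against about 40% loss, 60% of 128 should come to about 90. It comes to about 77. So at least one of the three figures (90, 40%, 128) is wrong, or the drop-out figure refers to something other than the T1 outcome.

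This sentence is the only justification given for the enrolment target. It tells readers that attrition of about 40% has been allowed for. If that attrition occurred at T1 and the trial found no difference, the result would be read against 80% power, which the calculation does not support at that loss.

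**Working it through.** **Inputs, all from the Sample size section unless noted:** d = 0.60 (SD = 1), two-sided alpha 0.05, power 80%, two-sample t test, 45 per group (90 in total), drop-out about 40%, enrolment 128; allocation 1:1 (Randomization section).

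**Step 1. Reproduce the plan's own figure.** Power comes from the non-central t distribution with n1 + n2 − 2 degrees of freedom and non-centrality d × √(n1·n2/(n1 + n2)).
- 45 per group: 80.4%.
- 44 per group: 79.5%.

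So 45 per group, 90 in total, is correct.

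**Step 2. Enrolment needed.** Randomised = evaluable / (1 − drop-out).
- 90 / (1 − 0.40) = 150. The stated figure is 128, which is 22 fewer.
- Patients left from 128 at 40% loss: 128 × 0.60 = 76.8, or 38.4 per arm. This is about 13 short of 90.
- Largest loss that 128 can absorb: 1 − 90/128 = 0.297, or 29.7%.

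The word approximately in the plan does not bridge the gap. At 35% loss, 90/0.65 = 138.5, so 139 patients would be needed, and 128 × 0.65 = 83.2 would remain.

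**Step 3. Power if 40% of T1 scores are missing.** Same formula, unadjusted, d = 0.6:

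| Per arm | Power |
|---|---|
| 38 | 73.3% |
| 38.4 | 73.7% |
| 39 | 74.4% |
| 45 (plan) | 80.4% |

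With 38.4 per arm, the effect detectable with 80% power is d = 0.648, against 0.60 in the plan.

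**Step 4. What covariate adjustment could give back.** If the baseline covariates have a multiple correlation r with T1 knowledge within arms, the residual SD shrinks by √(1 − r²), so the effective effect is 0.6/√(1 − r²). The article gives no value for r, so a range is shown as an assumption, at 38.4 per arm:

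| r | Power |
|---|---|
| 0 | 74% |
| 0.30 | 78% |
| 0.35 | 79% |
| 0.40 | 81% |
| 0.50 | 85% |

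Power reaches 80% at r of about 0.38 with 38.4 per arm, and about 0.39 with 38 per arm. In explained variance, 0.39² = 0.152 and 0.40² = 0.16, so about 15 to 16%.

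**Step 5. Possible origins of 128.** 90 × 1.40 = 126, which is two short. 90/0.70 = 128.6, which would fit if 40% had been written for 30%. The article does not allow a choice between them.

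**The case against.** Four points can be made for the plan.

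*The primary analysis is not the test used for sizing.* It adjusts for T0 knowledge and three other covariates, and a pre-test of the same knowledge may well predict the post-test. This stands as a real possibility: a moderate correlation would recover the loss. But the sample size calculation neither claims nor uses such a gain, and no correlation is reported.

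*Multiple imputation keeps everyone in the analysis.* Imputation at item level can rescue partly completed tests, and knowledge scores from other time points could help if they enter the imputation model. It can therefore recover some information. It does not fully replace T1 scores that were never observed, and patients who withdraw consent are left out altogether.

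*Loss at T1 may be far below 40%.* The Primary outcome section says T1 normally falls on the day of the consultation. The Data collection and management section allows at most 10 days and has questionnaires checked for completeness straight away. The 40% might describe loss by the 3-month follow-up. If T1 loss were no more than 29.7%, the primary comparison would keep its 90 patients. This stands as a condition on the power figures. It does not remove the contradiction, because the 40% is attached directly to a calculation whose named outcome is T1 knowledge.

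*The cause is not known.* A reader might infer that 90 was multiplied by 1.4 instead of divided by 0.6. The document does not support that as a fact: the product is 126, no derivation is given, and a misprint of 40% for 30% fits at least as well.

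**Conclusion.** The contradiction is certain and needs no outside assumption. On the plan's own figures, 128 randomised patients do not leave 90 at about 40% drop-out. They leave about 77, and 128 covers about 30%.

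The effect on power is conditional. If 40% of T1 scores are missing and the comparison is the unadjusted t test used for sizing, power for d = 0.6 is about 74%, a loss of about 6 percentage points. A reader might go further and conclude that the trial will fail to deliver 80% power. The documents do not support that, because the planned analysis is adjusted, T1 loss may be lower than 40%, and the 80% is stated for 90 participants rather than for what remains of 128. They do not support the opposite either, since the correlation that would restore 80% is nowhere given. The type I error rate and the choice of primary test are not affected.

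**What to change.** Keep 128 and correct the sentence in the Sample size section. First say whether the drop-out figure refers to missing T1 knowledge scores or to loss by T2. Then choose one of two statements:

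- (a) 128 allows for about 30% missing T1 outcomes (128 × 0.70 = 89.6, about 90). This is acceptable only if the sponsor can justify that rate; it should not be adopted merely because it fits 128.
- (b) Keep 40% and state about 74% unadjusted power for d = 0.6, rising to about 80% if the baseline covariates explain about 15 to 16% of the variance in T1 knowledge, with that condition marked as an assumption.

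For reference, holding both 40% loss and 80% unadjusted power would take 150 patients, but the correction does not require enrolling more. The cost is one reworded sentence and a stated figure that is slightly less favourable.

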#### Main analyses

All main analyses are based on the intention-to-treat (ITT) population, which includes all randomized patients except those who withdraw informed consent. Missing values will be assumed to be *missing at random* and replaced by multiple imputation using the *fully conditional specification method* [47]. When imputing multi-item instruments, imputation will be performed at the item level, and the total score will be calculated based on the imputed items [48]. Additionally, as sensitivity analyses, the results obtained for the ITT population will be compared to the results of a sample including only complete cases and to the results of a sample including only complete cases without serious protocol violations (per-protocol analysis).

All analyses will be carried out with SPSS 24. Descriptive analyses will be performed to describe sample characteristics.

Multiple linear regression analyses will be carried out to test the three hypotheses described. To test the main hypothesis, the influence of group membership (IG vs. CG) on the patient’s level of knowledge at T_1_ will be analyzed. The model controls for the following covariates: patient’s level of knowledge at T_0_, age, level of education, and study center.

Secondary outcomes will be analyzed using similar regression models. Additionally, to consider the usefulness of the PtDA from a provider perspective, group differences between physicians educating patients of the IG and the CG will be analyzed in terms of the physicians’ emotional and cognitive strain using the Mann-Whitney *U* test.

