### Participants

Patients with metastatic melanoma at stage 4 as well as patients at stage 3 whose tumor is not resectable and who will each receive first-line therapy will be eligible for the study. To participate, they must be older than 18 years and have sufficient knowledge of the German language. Patients with limited legal capacity or impairments in this respect, as well as patients with cognitive or physical impairments that affect the processing of the PtDA (e.g., impaired vision) and patients with severe psychiatric or mental illness, will be excluded from the study.

Patients who meet the inclusion criteria will be consecutively recruited by physicians in the day clinics of the study centers. The physicians will explain the course and purpose of the study and provide written information on the study. Patients willing to participate in the study will be required to give written informed consent (see Additional file 1). Patients’ consent to participate in the study can be withdrawn at any time and without giving a reason. The withdrawal will have no negative impact on the patients’ further treatment and will result in immediate termination of their participation in the study.

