### Randomization

After obtaining informed consent, randomization will be carried out by trained research assistants in the two study centers using a centralized web-based tool (Randomizer Software, Institute for Medical Informatics, Statistics and Documentation of the Medical University of Graz, www.randomizer.at). Block randomization is applied to guarantee equal sample sizes in each group in case the planned sample size is not achieved. The block size is specified in the web-based tool by the study coordinator and cannot be seen by physicians enrolling participants or research assistants assigning interventions. The allocation ratio for IG and CG is 1:1. Randomization is stratified by the study center. Due to the nature of this trial, blinding of the patients and physicians is not feasible.

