#### Delivery of the intervention

Patients randomized to the IG will be asked to use the PtDA on a tablet shortly before their medical consultation takes place. The processing of the PtDA takes approx. 35 min. Beyond the PtDA, patients of the IG will also receive an educational flyer and a note sheet to record their questions and thoughts in advance of the medical consultation. The educational flyer provides a summary of the most important contents of the PtDA. The differences between monotherapy and combination immunotherapy are presented as a so-called Option Grid [35]. Option Grids are tables comparing treatment options based on frequently asked questions. Previous research has shown that regardless of Internet access, many patients prefer print-based information in comparison with web-based information material [36]. Moreover, evidence regarding the satisfaction and competence of older patients when using web-based information, and tablets in particular, is mixed [37–39]. We assume that paper-based information will be a good supplement to the interactive web-based PtDA, not least because the flyer can be taken along to the medical consultation.

After finishing the PtDA, the patients’ individual treatment preferences assessed in the PtDA will be printed and made available to the attending physician to facilitate dialog between physician and patient during medical consultation.

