### Treatment as usual

CG patients will not have access to the PtDA. Instead, they will receive treatment as usual, which consists of a medical consultation on the treatment options available. It is possible that informational material, e.g., as provided by a pharmaceutical company, will be recommended or handed out, as the consultation varies depending on the personal communication style of the treating physician. Medical consultations will be recorded in both the CG and the IG (see Fig. 1). The resulting audio recordings will be transcribed and qualitatively evaluated in terms of SDM (see the “Key secondary outcomes” section).

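### The set labelled intention-to-treat drops every randomised patient who withdraws consent, so T1 knowledge scores already observed can be discarded after allocation

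*Protocol article*

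**What the plan says.** All references are to the protocol article.

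- **Main analyses.** One set serves all main analyses. It is called intention-to-treat and is one "which includes all randomized patients except those who withdraw informed consent". Missing values within that set are multiply imputed under MAR. The two sensitivity analyses use complete cases, and complete cases without serious protocol violations. The primary regression adjusts for T0 knowledge, age, education and centre.
- **Randomization.** "After obtaining informed consent, randomization will be carried out by trained research assistants". The same section states that "blinding of the patients and physicians is not feasible".
- **Participants.** "Patients’ consent to participate in the study can be withdrawn at any time and without giving a reason". Withdrawal "will result in immediate termination of their participation in the study". The section does not say that data already collected are to be deleted.
- **Data collection and management.** T1, the time of the primary outcome, is 0 to 10 days after the intervention. T2 is about 3 months after it, with 2 weeks either side of week 12 tolerated.

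**The concern.** An ITT set protects the comparison because membership is fixed at randomisation. Here membership depends on something that can only happen afterwards, when the patient already knows the arm. If withdrawal differs between arms and is related to knowledge, the two retained groups are no longer comparable in the way randomisation would make them.

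The sharper problem is one of timing. The rule has no time limit and covers all main analyses. A patient who filled in the T1 test and withdraws weeks later is taken out of the primary analysis, although the primary outcome is in hand. A patient who simply fails to return at T2 keeps the T1 score in the analysis. Two patients with the same observed primary data are therefore treated in opposite ways.

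**Working it through.** **1. Can the exclusion precede allocation?** No. Consent comes first and randomisation second, so a randomised patient can withdraw only after allocation.

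**2. How long is observed T1 data exposed?** T1 falls on days 0 to 10. T2 falls in weeks 10 to 14 (12 ± 2), that is days 70 to 98. The gap runs from 70 − 10 = 60 days to 98 − 0 = 98 days. Withdrawal at any point in it removes a recorded primary outcome. T1 is usually on the day of the consultation, so most of the follow-up during which a patient could withdraw lies after T1.

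**3. Does anything in the plan restore these patients?**

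| Planned step | Set used | Restores withdrawers? |
|---|---|---|
| Multiple imputation | The set as defined | No |
| Complete cases | Narrower | No |
| Complete cases without serious violations | Narrower still | No |

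**4. How large could the effect be?** The document gives no rate of consent withdrawal, so the following are assumptions. Let w be the share of an arm excluded, and δ the amount (in SD) by which excluded patients would score below retained patients in that arm. The retained mean exceeds the full-arm mean by w × δ. Hence

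bias = (w × δ) in the intervention group − (w × δ) in the control group.

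With withdrawal in the intervention group only, 128 / 2 = 64 randomised per arm, SE = √(1/[64(1 − w)] + 1/64), a normal approximation and no covariate adjustment:

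| w | δ | Bias (SD) | Share of d = 0.6 | Two-sided type I error |
|---|---|---|---|---|
| 5% | 0.25 | 0.013 | 2% | 0.051 |
| 5% | 1.0 | 0.05 | 8% | 0.059 |
| 10% | 0.5 | 0.05 | 8% | 0.059 |
| 10% | 1.0 | 0.10 | 17% | 0.085 |
| 20% | 0.5 | 0.10 | 17% | 0.083 |
| 20% | 1.0 | 0.20 | 33% | 0.187 |

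Worked line: w = 0.10, δ = 0.5 gives bias 0.10 × 0.5 = 0.05 SD, SE = √(1/57.6 + 1/64) = 0.182, and bias/SE = 0.275.

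Equal w and δ in both arms give zero. The same loss in the control group only reverses the sign. The yardstick d = 0.6 is the plan's own: its 45 per group reproduces with a two-sample t test (44.59, rounded up; power 0.804).

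**5. What does covariate adjustment do?** If withdrawal depends only on T0 knowledge, age, education or centre, and the linear model is right, the adjusted arm coefficient is not biased by the loss. Only the part of δ left after adjustment counts, so the table overstates the effect to that extent.

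**6. What would keeping the patients change?**

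- *Withdrawal after T1:* the observed score is used, and the loss for the primary analysis disappears.
- *Withdrawal before T1:* imputing T1 under MAR from the same covariates places these patients, on average, on the surface fitted to the retained patients. The arm coefficient hardly moves, and selective loss that the covariates do not explain remains.

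**The case against.** The strongest case on the other side has five parts.

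- **The definition is disclosed beside the label.** No reader is misled about who is analysed. That is so, but disclosure does not keep the patients in, and the label still promises more than the set delivers.
- **The consent form is not shown.** It, or data protection law, may require deletion when consent is withdrawn. This stands for patients who revoke use of their data, for whom exclusion may be unavoidable. The text shown, however, says only that participation ends, and the exclusion is not limited to revoked data use.
- **Detail is commonly left to the full protocol or SAP.** True of withdrawal categories and reporting by arm. The exclusion itself is stated outright and applies to all main analyses.
- **The model adjusts for likely drivers of withdrawal.** This stands in part: it removes bias running through those covariates and nothing else.
- **MAR imputation of patients without T1 changes almost nothing.** This stands. It narrows the avoidable harm to patients who withdraw after T1, and it means that a wider set needs a sensitivity analysis that departs from MAR.

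A reader might also infer that the extra task, for which the plan says "The processing of the PtDA takes approx. 35 min", drives patients out of the intervention group alone and so biases the result in favour of the decision aid. The document does not support that. Control patients also complete questionnaires and have consultations recorded, and they know that they were not given the aid. An intervention patient who stops using the tablet need not withdraw consent. Excessive strain is handled as a documented deviation with its own sensitivity analysis.

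**Conclusion.** The concern holds in a limited form. The main set is a modified ITT set under an ITT label. Its exclusion is post-randomisation, may differ by arm, and as written discards T1 scores already observed in patients who withdraw between T1 and T2. No planned analysis tests the effect.

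This is a risk, not a demonstrated bias. Size and direction are unknown because no withdrawal rate is given. The 0.01 to 0.20 SD range is illustrative: it rests on assumed loss in one arm and assumed gaps, before adjustment. With few or balanced withdrawals the effect is small.

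It would be tempting to take the assumed drop-out of about 40% as the share removed. It is not: the rule removes only those who withdraw consent, while other drop-outs stay in the set and are imputed.

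**What to change.** - Define the ITT set as all randomised patients, analysed in the arm to which they were allocated.
- Separate stopping participation from revoking use of data.
- Where the consent form permits, keep everything collected up to withdrawal and treat later values like any other missing data.
- Exclude only patients who revoke use of their data, and report their number and timing by arm.
- Add a sensitivity analysis over all randomised patients that allows departures from MAR, using allocation alone for those whose data may not be used. MAR imputation by itself will not correct selective loss before T1.
- If the present exclusion has to stay, call the set modified ITT.

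The cost is a revised population definition, a check of the consent form and a little more analysis. Sample size and trial procedures do not change.

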### Outcomes

#### Primary outcome

The primary outcome for hypothesis 1 is the patient’s level of knowledge after the intervention, since it is a crucial prerequisite for a common therapeutic decision that patients have understood the risks and benefits of different therapeutic options [25]. Patients’ knowledge will be assessed directly after the intervention (T_1_), in other words, after the medical consultation, and usually on the same day as the medical consultation. Knowledge about first-line treatment options for metastatic melanoma will be assessed with a self-developed, piloted knowledge test (see Additional file 3). This test consists of 10 multiple choice questions in single-selection and multi-selection formats. The scores of the individual tasks are weighed and added up to a total score, which ranges between 0 and 40. Higher scores indicate a higher level of knowledge about treatment options. The reliability of the test, according to an unpublished preliminary study (*N* = 24), is good, with <.8. In addition to T_1_ (primary outcome), patients’ knowledge will also be assessed before the intervention (T_0_) and at the 3-month follow-up (T_2_). T_0_ serves to statistically control for prior knowledge (see Fig. 1).

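### The item-level imputation rule has no exception for the knowledge test, so it credits expected points for questions left blank on a returned primary-outcome test

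*Protocol article*

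**What the plan says.** The protocol article, Main analyses, states the mechanism and the method together: "Missing values will be assumed to be *missing at random* and replaced by multiple imputation", by fully conditional specification. It then fixes the level: "When imputing multi-item instruments, imputation will be performed at the item level, and the total score will be calculated based on the imputed items". No instrument is excepted. The planned sensitivity analyses are complete cases and complete cases without serious protocol violations.

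The Primary outcome section describes the instrument: "This test consists of 10 multiple choice questions in single-selection and multi-selection formats". Question scores are weighted and summed to a total between 0 and 40, and "Higher scores indicate a higher level of knowledge about treatment options". The T1 score is the primary outcome and the T0 score is a covariate in the primary model. The test form is in Additional file 3, which is not shown. The article does not say how a blank is scored or whether a don't-know option exists.

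The Data collection and management section has a research assistant check filled-in questionnaires at once for completeness, with the aim of avoiding missing values. It also says that some questionnaires go by post, without saying at which time points.

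**The concern.** Item-level imputation suits a rating scale such as the SwD, where a skipped item has a plausible unobserved value. On a right/wrong test a blank is often itself the result. If a question is blank because the answer is not known, missingness depends on the item's own value, and filling it from patients who answered credits knowledge that was not demonstrated.

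For example, suppose that questions carry 4 points each (an assumption). A patient with 7 correct and 3 blank has shown 7 × 4 = 28 points. If imputation adds about 2 to 3 points per blank, the analysed score becomes 34 to 37. On multi-selection questions an unticked option and a non-response may also look alike on paper, and the rule does not separate them.

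At stake is the primary contrast. Patients who know less have more questions to leave blank. If the decision aid works, that is the control arm at T1, so the rule could add more points there. Neither planned sensitivity analysis would reveal this. Both drop patients with gaps, which under this mechanism preferentially removes the less informed, and neither scores a blank as 0.

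**Working it through.** **1. The plan's own figure.** The Sample size section says "PtDAs improve the level of knowledge with an effect size of *d* = 0.60" and that "a case number of *n* = 45 participants per group (total = 90) is sufficient to detect a statistically significant effect of *d* = 0.6" with 80% power at two-sided 5%. The noncentral t distribution gives 45 per group with power 0.804, so the figure reproduces. The normal approximation gives 44. All power figures in steps 2 and 3 are for a two-sample t test with 45 per arm.

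**2. Expected effect of the rule, arm by arm.** Assumptions, because the article gives none of these: equal item weights, SD 7, control mean 20 and intervention mean 24.2 with blanks scored 0. The difference is then 4.2 points and d = 4.2/7 = 0.60. For an arm with mean m and blank share b:

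- share correct among answered items: p = (m/40)/(1 − b)
- points added by imputation: 40 × b × p

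For 5% blanks in control and 2.5% in intervention:

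- control: p = 0.50/0.95 = 0.526, added 40 × 0.05 × 0.526 = 1.05
- intervention: p = 0.605/0.975 = 0.621, added 40 × 0.025 × 0.621 = 0.62
- difference: 4.2 + 0.62 − 1.05 = 3.77, d = 3.77/7 = 0.54, power 0.71

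| Blanks control / intervention | Added, control | Added, intervention | Difference | d | Power |
|---|---|---|---|---|---|
| 2% / 1% | 0.41 | 0.24 | 4.04 | 0.58 | 0.77 |
| 5% / 2.5% | 1.05 | 0.62 | 3.77 | 0.54 | 0.71 |
| 10% / 5% | 2.22 | 1.27 | 3.25 | 0.46 | 0.59 |
| 5% / 5% | 1.05 | 1.27 | 4.42 | 0.63 | 0.84 |
| 10% / 9% | 2.22 | 2.39 | 4.37 | 0.62 | 0.83 |
| 5% / 10% | 1.05 | 2.69 | 5.84 | 0.83 | 0.97 |

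Scores rise in every row, but the difference shrinks only if b × p is larger in the control arm. In these scenarios control blanks must exceed intervention blanks by a factor of about 1.1 to 1.3. If the imputation model ignored group, any excess of control blanks would shrink the difference and equal shares would leave it at 4.20.

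**3. Simulation with blanks only on unknown items.** Settings: 10 questions of 4 points, 45 per arm, 200 runs, no guessing, 5 imputations by logistic fully conditional specification on the rest score and group. Starting differences vary between rows through simulation noise, so compare within a row.

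| Skipping of unknown items, control / intervention | Blank items | Difference, blank = 0 → imputed | d | Power |
|---|---|---|---|---|
| 5% / 5% | 2.5% / 1.8% | 5.67 → 5.64 | 0.61 → 0.61 | 0.81 → 0.81 |
| 10% / 10% | 4.9% / 3.5% | 5.95 → 5.87 | 0.64 → 0.64 | 0.85 → 0.85 |
| 30% / 30% | 14.9% / 10.6% | 5.70 → 5.32 | 0.61 → 0.60 | 0.82 → 0.80 |
| 30% / 15% | 14.9% / 5.3% | 5.94 → 4.21 | 0.63 → 0.46 | 0.84 → 0.57 |
| 15% / 30% | 7.7% / 10.6% | 5.90 → 7.15 | 0.63 → 0.80 | 0.84 → 0.96 |

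With equal skipping, control blanks are about 1.4 times intervention blanks (14.9/10.6). That is above the step 2 threshold, which is why the difference falls slightly.

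**4. A second simulation of the same mechanism** (equal skipping, 45 per arm) gave a somewhat larger cost. Power was 0.81 with blank = 0 and 0.78 imputed at about 4 to 5% blanks, and 0.86 against 0.78 at 10% / 7%.

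**5. Accidental skips.** With the step 3 settings but 10% of all items blank regardless of knowledge, the true difference of 6.07 becomes 5.43 with blank = 0 and 6.04 imputed. Power is 0.82 and 0.86. In the second simulation, at 5% accidental skips, power is 0.78 with blank = 0 and 0.84 imputed.

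**The case against.** **The article may only be silent.** It never says that an unanswered knowledge question is a missing value, and a scoring key in Additional file 3 could already give it 0. This stands in part: if the key does so, or if patients use a don't-know option, the bias is near zero. But the Data collection and management section treats gaps on filled-in questionnaires as missing values, and the knowledge test is one of them. Main analyses then imputes missing items on every multi-item instrument. Read as written, the rule reaches the knowledge test.

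**Blanks will be few.** This largely stands. Forms are checked at once, and T1 usually falls on the day of the consultation. It limits the size but does not settle how a remaining blank should be treated.

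**Scoring 0 is not neutral.** This also stands. For a question skipped by oversight, imputation is appropriate and 0 is the biased choice (step 5). Scoring 0 also separates patients who skip from patients who guess.

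**A stronger reading.** A reader might infer that the rule necessarily shrinks the group difference, and by a tenth or more. The documents do not support that. They give no blank rate, do not say that blanks mean ignorance, and do not say that control patients leave more. Step 2 shows that equal blank shares can widen the difference, and step 3 that more skipping in the intervention arm does. A simulation with 25% guessing success does give losses of 6% to 27% against blank = 0, when 10% to 50% of unknown items are blank (5.43 to 5.11, and 6.03 to 4.39). Part of that gap comes from the comparator, because scoring blanks 0 removes lucky guesses and so enlarges the reference difference. Rescaled to a test without blanks, the references are 5.43 × 0.75/0.775 = 5.25 and 6.03 × 0.75/0.875 = 5.17, and the losses are about 3% and 15%.

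**The bias is conservative.** That is true only in the direction towards no effect. If intervention patients skip more, imputation exaggerates the difference.

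**Conclusion.** The point holds as a misfit between a stated rule and the primary endpoint. Applied literally, the rule adds points for unanswered questions: about 0.4 points per arm at roughly 2% blanks, 0.8 to 0.9 at roughly 4 to 5%, and 3.0 (control) and 2.6 (intervention) at 15% / 11%. These figures assume that a blank means not known and that items carry equal weight.

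The effect on the contrast is conditional. If skipping of unknown items is equally common in both arms, it is slight at a few percent of blanks: between nothing and about 0.03 of power across the two simulations. A serious loss, such as d from 0.63 to 0.46, needs control patients to skip clearly more readily. The reverse pattern inflates the effect. Towards no effect is the most plausible direction if the aid works, but the documents do not establish it. The T0 covariate is open to the same inflation; since T0 precedes the intervention, this should weaken the adjustment more than it shifts the contrast.

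The change is worth making because the treatment of blanks on the primary test should be settled before the data are seen, and no planned sensitivity analysis covers it.

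**What to change.** In Main analyses, exempt returned knowledge tests from item-level imputation. State that on a returned test at T0, T1 or T2 an unanswered question scores 0 and an unticked option counts as not selected, and that multiple imputation of knowledge applies only where the test was not returned. Keep item-level imputation for the SwD and the other rating scales. Report the number of blank questions by arm and time point, and give the version with imputed blanks as a sensitivity analysis.

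If Additional file 3 already scores blanks as 0 or offers a don't-know option, Main analyses only needs aligning with it.

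The cost is one sentence and one extra analysis, with no new data, patients or procedures. The downside is that a question skipped by accident scores 0 even if the patient could have answered it, which slightly dilutes the contrast. The completeness check should keep that rare, and the sensitivity analysis would show it.
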